## Abstract

**Background:**

The high occurrence and under-treatment of clinical depression and behavioral and psychological symptoms of dementia (BPSD) within aged care settings is concerning, yet training programs aimed at improving the detection and management of these problems have generally been ineffective. This article presents a study protocol to evaluate a training intervention for facility managers/registered nurses working in aged care facilities that focuses on organisational processes and culture as well as knowledge, skills and self-efficacy.

**Methods:**

A Randomised Control Trial (RCT) will be implemented across 18 aged care facilities (divided into three conditions). Participants will be senior registered nurses and personal care attendants employed in the aged care facility. The first condition will receive the training program (*Staff as Change Agents – Enhancing and Sustaining Mental Health in Aged Care*), the second condition will receive the training program and clinical support, and the third condition will receive no intervention.

**Results:**

Pre-, post-, 6-month and 12-month follow-up measures of staff and residents will be used to demonstrate how upskilling clinical leaders using our transformational training approach, as well as the use of a structured screening, referral and monitoring protocol, can address the mental health needs of older people in residential care.

**Conclusions:**

The expected outcome of this study is the validation of an evidence-based training program to improve the management of depression and BPSD among older people in residential care settings by establishing routine practices related to mental health. This relatively brief but highly focussed training package will be readily rolled out to a larger number of residential care facilities at a relatively low cost.

**Trial registration:**

Australia and New Zealand Clinical Trials Register (ANZCTR): The Universal Trial Number (UTN) is U1111-1141-0109.

## Background

Mental health disorders are common in aged care settings. A review of the literature reported that almost one third of aged care residents have depressive symptoms, while an estimated 10% of aged care residents meet criteria for a current diagnosis of Major Depressive Disorder (MDD) [1]. Despite the awareness of the high prevalence of depression in the aged care population, the high occurrence and under-treatment of depression within aged care settings is concerning, with studies indicating that depressive illness is associated with increased mortality risk of chronic disease, and the requirement for higher levels of supported care [2].

In addition, more than half of the aged care population is estimated to demonstrate Behavioural and Psychological Symptoms of Dementia (BPSD), such as agitation, verbal and physical aggression, sleep disturbance, and wandering [1]. Research has demonstrated that these disturbances are not well managed by staff in the aged care sector [3]. This is of particular concern as the failure to adequately care for older people with BSPD is associated with serious adverse outcomes, including increased falls and injury, the use of restraints, social isolation, admission to a psychiatric inpatient ward, and stress and burnout among care staff [4,5].

Aged care staff have the potential to play a key role in the detection, assessment, management, and ongoing monitoring of mental health disorders among their care recipients. However, research suggests that these staff receive little training in mental health and commonly hold misconceptions about disorders such as depression and BPSD [6,7], and as a result, have demonstrated poor skills in managing residents with these disorders [8,9]. In the project described in this paper, senior clinical and organisational leaders as well as senior Registered Nurses (RNs) and Personal Care Assistants (PCAs) will participate in a transformational training program to better detect and manage depression and BPSD. The program also focuses on how to improve workplace climate and effective leadership in mental health practices. Transformational training is an approach that is specifically designed to address factors related to organisational leadership and workplace climate, and so ensure that organisational barriers to the effective implementation of training into practice are resolved [10-13]. Research has confirmed that transformational training leads to increased trust, commitment, staff engagement, perceived management support, and cohesion [11,12], which are fundamental to effective and sustained change in organisational practices [13]. This, in turn, will allow these staff to encourage, inspire and motivate other staff to internalise and routinely use strategies to manage depression and BPSD and referral practices.

The aim of this paper is to outline the hypotheses of the current study, to describe the method utilized in the study design, and the development and proposed evaluation of the *Staff as Change Agents Program* - an educational and transformational training program for professional care staff in residential aged care.

### Hypotheses and expected outcomes

It is hypothesised that the transformational training program will be superior to care as usual in terms of:

● Organisational strategies to manage depression and BPSD, and

● Staff knowledge and skills in the provision of mental health care;

● Workplace climate factors such as staff trust, teamwork/cohesion, communication and supportive workplace relations;

● Staff factors such as stress, job satisfaction, and turnover; and

● Severity of resident depression and BPSD.

It is also hypothesised that supplementing the transformational training program with clinical support from a mental health nurse specialist will lead to greater benefits than the same program without clinical support.

## Methods

### Study design

A cluster randomised controlled design will be employed in this study, with participating facilities allocated to one of three conditions. The first condition will implement the training program in six facilities. The second condition will involve the implementation of the training program in another six facilities with the additional provision of clinical support to assist staff in these facilities with the roll out of the strategies and training offered in the program. Clinical support will be provided by an experienced and appropriately trained mental health specialist who will be situated within each facility for approximately one day per week for a six month period. The third condition will include six facilities that will participate in our project as a ‘care as usual’ control group. All participating facilities will be randomly allocated to one of these three conditions, and the control condition will have access to the training program at the end of their participation in the no-intervention condition.

### Target population

A total of 108 staff will participate in the study, including 54 senior staff (i.e., 3 facility managers and/or RNs from each of the 18 facilities) and 54 senior PCAs (i.e., 3 PCAs from each of the 18 facilities).

A total of 360 residents will be recruited to participate in the study. Across each of the 18 facilities, 10 residents with dementia who present with BPSD will be selected through consultation with facility staff. Similarly, 10 residents with undetected and untreated depression will be recruited across all 18 facilities. Initially depressed residents will be identified through examination of resident files and existing documentation collected for every Australian resident (known as the Aged Care Funding Instrument [ACFI]), which includes a depression screening instrument – the Cornell Scale for Depression in Dementia [14]. However final recruitment will be based on a Research Fellow conducting the Cornell Scale and selecting residents with a Cornell score of 8 and above (must include low mood in symptom count).

### Intervention program

The four-session *Staff as Change Agents – Enhancing and Sustaining Mental Health in Aged Care* program was developed based on evidence from the researchers’ previously established training programs, previous findings in relation to organizational barriers in aged care, and current programs using transformational training in other settings [15]. An additional booster session focussed on organizational barriers to mental health care is also included four weeks after the completion of the program. The transformational training program is a multi-faceted approach that trains staff in the detection and management of depression and BPSD, and then develops leaders’ abilities to support staff through organisational change. Specifically, it trains staff in how to encourage, inspire and motivate other staff to internalise and routinely use strategies to manage depression and BPSD and referral practices. It enables staff to see these strategies as important and meaningful to residents and the teams themselves. The training also highlights the relational aspects of teams, providing leaders with training in developing trust, cohesion and communication amongst team members (see Table 1). This training approach is vastly different from the way that aged care teams typically function at present, with for example, managers often engaging in transactional behavior that try to gain staff compliance via offering rewards, or punishing deviations from procedures – a managerial style that results in emotional exhaustion, staff burnout, and poor adherence to workplace initiatives [16].

**Table 1 T1:** **Delivery format and content of the *****Staff as Change Agents – Enhancing and Sustaining Mental Health in Aged Care *****training program**

**Session 1**	**Session 2**	**Session 3**	**Session 4**	**Booster session**
• Depression and Workplace Environment	• Behavior of Concerns Associated with Dementia	• Staff as Change Agents	• Sustaining Mental Health in Aged Care	• Approximately 4 weeks after session 4
• detect symptoms of depression and how to recognise masked symptoms of depression	• describe and discuss challenging behavior of residents with dementia	• explore workplace environment factors for improving mental health protocols	• identify key issues that lead to resistance to change in the detection and management of depression and BPSD	• review skills and instruments introduced in sessions one and two
• adopt effective communication and psychosocial strategies when dealing with residents with depression	• explore workplace challenges	• examine workplace outcomes, strengths and gaps		• revisit staff competencies in using these instruments
• use checklist and refer resident on to a senior staff member	• review “Assessment & Management Tool for Staff”	• define effective leadership behavior		• additional training using the Cornell Scale for Depression in Dementia and the assessment tool for staff to better manage
• administer Cornell Scale for Depression in Dementia	• discuss benefits and challenges using this assessment	• discuss key attributes and behavior for facilitating change		
define workplace environment and the factors that influence staff attitudes and behavior	explore how staff can implement this assessment tool using the enabling factors of effective communication, trust, teamwork and cohesion			challenging behavior
• identify facility’s work environment				• review mental health protocols and the sustained implementation of the instruments

### Evaluation of the training program

#### Evaluation measures for aged care staff

All of the following measures will be completed by aged care staff at the 18 residential facilities at pre-intervention, post-intervention, 6-month and 12 month follow-up (or equivalent time for the control group).

1. *Knowledge of Late Life Depression Scale – Revised*. Developed by our team with a sample of 320 care staff in our previous study, an expanded version of this questionnaire will be used to measure staff knowledge of depression and BPSD ([name] et al., in press). This instrument was validated with confirmatory factor analysis and has good psychometric properties. It was also sensitive to change in knowledge of depression in our pilot evaluation [4].

2. *Confidence in Working with Depressed Older People Scale.* This four-point Likert scale will be used to measure how confident staff members felt working with people with depression: ‘Not at all confident’ to ‘Very confident’.

3. *Self-Efficacy in Working with Depression Scale*. Developed in our previous study, an expanded version of this questionnaire will be used to measure staff self-efficacy in caring for residents with depression and dementia [17]. Three aspects are measured, reflecting the tasks typically required of staff in working with depressed people: ‘Detecting Depression’, ‘Responding to Depression’, and ‘Communicating with Patients’. Each subscale has strong internal reliability (Cronbach’s α > .90, and has demonstrated sensitivity to change [17].

4. *Strains in Nursing Care and Work Scale*[17]. This questionnaire contains situations and thoughts or feelings which can arise when caring for people with dementia. Staff members will rate how often they encounter these situations and feelings and, when they occur, how much stress they experience.

5. *Working Environment Scale.* This scale will be used to assess aspects of the work environment, including emotions, job satisfaction, work-related problems, views about the organisation and turnover intention.

6. *Organisational Climate Questionnaire*. This 40-item questionnaire will be used to assess eight workplace climate variables [18]. Each of these subscales has good internal consistency (α > .80).

#### Evaluation measures for aged care residents

1. Depression referral rates to primary and specialist health services will be recorded at each data collection period. Participating staff will be asked to keep records of all such referrals. This will be validated by an examination of files on a bi-monthly basis for 12 months after the implementation of the MHCTC program.

2. The management of depression and BPSD will be assessed through a review of the residents’ files by a blinded assessor who is familiar with aged care documentation. The documentation reviewed will include the resident care plan, progress notes, medical notes and medication charts. The review will focus on records of assessment, monitoring of symptoms, medical referrals, pharmacological and non-pharmacological treatment and nurse-led strategies to manage symptoms. The review will be conducted on a bi-monthly basis for 12 months after the implementation of the MHCTC program.

3. Severity of BPSD will be assessed using the Cohen-Mansfield Agitation Inventory [21], rated by two facility staff members who typically observe the resident on the morning and afternoon shifts.

4. Severity of depression will be assessed using the Cornell Scale for Depression in Dementia [14] rated by a blinded Research Fellow.

### Procedure

Staff participants in all facilities, including the control condition, will be asked to complete survey measures prior to commencing the program and again at the conclusion of the program and at 6 and 12 month follow-up.

For the staff in the training program conditions, each training session will take approximately two hours to complete during work time, and will include discussions, role plays and handouts. The clinical support (for the six facilities in training and clinical support conditions) will assist staff in implementing the training received in the detection and management of depression and BPSD. Further, the clinician will work with staff to implement the strategies in the program to address the organizational barriers that act against the mental health needs of residents being addressed. Participants will also be asked to complete work practice activities in between sessions. The protocol adopted for the study is outlined in Figure 1.

**Figure 1 F1:**
[figure not shown]
Staff as change agents – enhancing and sustaining mental health in aged care.

## Results

### Data analysis

For analysis of differences in facilities at baseline, analysis of variance (ANOVA) will be used, with Fisher’s Exact test for analysing categorical variables. For changes over time, repeated measures multiple analysis of covariance (MANCOVA; controlling for group baseline scores on outcome measures) will be used for our continuous measures associated with staff outcomes. Longitudinal Configural Frequency Analysis (CFA) will be used to analyse change in categorical variables such as number of depression and BPSD referrals prior, immediate post training, at 6-month and at 12-month training follow-up. CFA is a technique analogous to repeated measures MANCOVA that allows for the estimation of trends and group differences over time but for categorical variables. Allowing for a 20% attrition rate – a rate of attrition common in our past studies – we have calculated that we will maintain at least 28 staff and 96 residents per condition at 12-month follow-up. Based on our estimated sample size in each of the conditions at 12-month follow-up, and with the expectation of a small-to-moderate effect size d = .20, the power of the analyses for aged care resident data is calculated at 0.99, and for the staff data at .91 at the two-sided significance level of α = .05 for both our mean difference testing and categorical analyses [22].

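### Whole facilities are randomised, but the two methods named for change over time, and the power statement, treat individuals as independent, so type I error exceeds .05 if members of a facility are correlated

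*Protocol article*

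**What the plan says.** Study design, in the protocol article, sets the unit of allocation: "A cluster randomised controlled design will be employed in this study, with participating facilities allocated to one of three conditions". Each condition has six facilities ("The first condition will implement the training program in six facilities" and likewise for the other two), and "All participating facilities will be randomly allocated to one of these three conditions".

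Target population gives the numbers inside those clusters: "A total of 108 staff will participate in the study, including 54 senior staff", which is 6 per facility, and "A total of 360 residents will be recruited to participate in the study", which is 20 per facility (10 with BPSD and 10 with depression).

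Data analysis names two methods for change over time. For continuous staff outcomes, "repeated measures multiple analysis of covariance (MANCOVA; controlling for group baseline scores on outcome measures) will be used". For categorical outcomes such as referrals it names longitudinal configural frequency analysis (CFA). No facility effect, cluster-robust variance, cluster-level summary, ICC or design effect appears there or elsewhere in the article. The power statement works from 28 staff and 96 residents per condition at 12 months, "with the expectation of a small-to-moderate effect size d = .20", at the "two-sided significance level of α = .05", and is said to cover both the mean comparisons and the categorical analyses. No model is named for the continuous resident scales (depression and agitation severity).

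**The concern.** Both hypotheses, training against usual care and training with against without clinical support, are comparisons of one set of six facilities with another. Chance differences between facilities are therefore part of the error against which an effect must be judged. MANCOVA and CFA, as named, take each participant as an independent observation and leave that part out.

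The article's own account makes some within-facility correlation likely. The training is meant to act through leadership, trust, cohesion and climate, which colleagues share. Several staff scales measure exactly those things. The mental health specialist works inside each supported facility. The facility's own staff rate agitation and record referrals.

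At stake is a chance difference between facilities being reported as an effect of training or of clinical support, in a trial whose results are intended to inform policy and service planning.

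**Working it through.** **Inputs from the article.** 6 facilities per condition; 36 staff and 120 residents per condition recruited; 20% attrition; two-sided alpha .05; d = .20. The ICC is not given; I assume .01, .05 and .10.

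**The plan's own figures.** Retention agrees: 36 × 0.8 = 28.8 staff and 120 × 0.8 = 96 residents per condition. The stated power does not follow from d = .20. With independent individuals, the noncentrality is 0.20 × √(n/2). That is 0.20 × √48 = 1.39 for residents (power 0.28) and 0.20 × √14 = 0.75 for staff (power about 0.11), against the stated 0.99 and .91. The staff figure can be matched if .20 is read as the ANOVA effect size f in a repeated-measures analysis (2 groups, 3 occasions, correlation 0.5: 0.910 for staff, above 0.99 for residents). That is a separate problem. What matters here is that no variant tried that reaches the stated figures contains a design effect.

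**Cluster size at 12 months.** Staff 28/6 = 4.67; residents 96/6 = 16.

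**Formulas**, for an unadjusted single-occasion test that ignores facility:
- Design effect DE = 1 + (m − 1) × ICC; true SE / naive SE = √DE.
- Pairwise type I error = 2 × [1 − Φ(1.96/√DE)].
- Three-group type I error ≈ P(χ² on 2 df > 5.99/DE) = .05^(1/DE).

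| | ICC | DE | SE ratio | Pairwise | Three-group |
|---|---|---|---|---|---|
| Staff, m = 4.67 | .01 | 1.037 | 1.02 | 5.4% | 5.6% |
| | .05 | 1.183 | 1.09 | 7.2% | 8.0% |
| | .10 | 1.367 | 1.17 | 9.4% | 11.2% |
| Residents, m = 16 | .01 | 1.15 | 1.07 | 6.8% | 7.4% |
| | .05 | 1.75 | 1.32 | 13.8% | 18.1% |
| | .10 | 2.50 | 1.58 | 21.5% | 30.2% |

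If each resident scale is analysed only in its own group of 10 per facility, m = 10 × 0.8 = 8. The pairwise error is then 5.8%, 9.2% and 13.3%.

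**Simulation check** (20,000 null trials per setting, six facilities per condition). With 5 staff per facility: pairwise 5.5%, 7.5%, 9.7%; three-group 5.8%, 8.1%, 12.2%. With 16 residents: pairwise 6.5%, 13.4%, 21.0%; three-group 7.3%, 18.1%, 30.1%. An analysis of facility means stayed between 4.7% and 5.3% in all these settings.

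**Power once facility is respected** (d = .20, effective n = n/DE, t on 10 df for six against six). Residents 0.22, 0.16 and 0.13; staff 0.10, 0.10 and 0.09 at ICC .01, .05 and .10.

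**The case against.** **A condensed article may leave model detail to an analysis plan.** This is true of the random-effects structure and the degrees-of-freedom method. It does not cover the present case. The article does not merely omit clustering; it names methods, and a power basis, that do not fit its own design. A later plan would have to replace them.

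**The percentages are not the planned analysis.** This stands. They come from a single-occasion unadjusted test, whereas the plan is baseline-adjusted, repeated and multivariate, and CFA was not simulated. Baseline adjustment can remove stable facility differences. Facilities can still diverge after baseline, and an intervention delivered facility by facility gives a reason to expect it. The relevant ICC is the one left after adjustment, and it is unknown.

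**The quoted method covers staff only.** This also stands. The larger resident figures apply only if residents are tested as individuals. The power statement assumes so, but the article names no model for the continuous resident scales.

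Three stronger readings are tempting and not supported:
- A reader might infer that every named test is invalid. The ANOVA and Fisher's exact test are assigned to comparing facilities at baseline; facility is the factor compared, and they do not test the intervention.
- A reader might take the group baseline scores in the MANCOVA wording to mean a condition mean, fully confounded with condition. Such a covariate could not be fitted alongside condition. Loose wording for baseline adjustment is the more plausible reading.
- A reader might conclude that the trial's false-positive rate is 20 or 30%. That needs the resident setting, an ICC of .10 and no benefit from adjustment.

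**Conclusion.** Wrong as written. The fault is confined to MANCOVA and CFA as tests of the intervention, and to the power statement that shares their assumption. For any positive residual ICC with more than one participant per facility, standard errors are too small and the error rate exceeds .05; at an ICC of zero there is no inflation. For staff, the only group with a named continuous-outcome method, the inflation is modest: about 5.5% at ICC .01, rising to 9 to 12% at .10. For residents it could be large, about 7% rising to 22 to 30%, but those figures are illustrative. All sizes rest on assumed ICCs, equal facility sizes and an unadjusted test. The direction does not depend on the particular ICC chosen.

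**What to change.** Analyse staff and resident outcomes with a method that respects facility as the unit of randomisation. Two choices are sound:

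1. A linear mixed model with condition by occasion, the individual's own baseline score, a facility random intercept, a participant random effect and small-sample degrees of freedom (Kenward-Roger or Satterthwaite; about 18 − 3 = 15 between facilities). Use the matching generalised mixed model for counts and binary items.
2. An analysis of baseline-adjusted facility-level summaries, 18 values per outcome and occasion.

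Name the model for the continuous resident scales as well. Report the ICC for each outcome. Restate the power with an assumed ICC range and six facilities per condition.

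No new data or change of design is needed to correct the analysis. The costs are more analysis work, wider confidence intervals and a much less favourable stated power. If separate models replace one multivariate test across ten staff instruments, a multiplicity rule is also needed.

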## **Discussion**

Organisational barriers clearly limit the effective translation of skills into the routine care practices of staff to address depression and BPSD among residents in aged care facilities. The project described in this article will implement and evaluate two interventions that are designed to address the organisational barriers to mental health care (transformational staff training program and clinical support). It is expected that the project will demonstrate that with the transformational training program, a more accurate identification of depression and the causes of BPSD will ensue, resulting in appropriate treatment being delivered. This will result in less distress and improved quality of life for both residents and staff, and improve the job satisfaction of aged care staff, thereby reducing staff turnover. It will also determine the extent to which external specialist clinical support is required to produce optimal outcomes, an issue that to date has not been clearly determined, and which is essential for appropriate service planning.

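### The repeated-measures MANCOVA for staff outcomes conventionally drops anyone missing a wave, although leaving is itself expected to depend on training, and turnover is measured only as intention

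*Protocol article*

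**What the plan says.** Five places in the protocol article bear on this.

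- **Hypotheses and expected outcomes:** training is expected to be superior to usual care on several fronts, one of which is "Staff factors such as stress, job satisfaction, and turnover; and".
- **Discussion:** the expected mechanism is given. The project should "improve the job satisfaction of aged care staff, thereby reducing staff turnover".
- **Evaluation measures for aged care staff:** the scales "will be completed by aged care staff at the 18 residential facilities at pre-intervention, post-intervention, 6-month and 12 month follow-up". The Working Environment Scale covers aspects of the work environment, "including emotions, job satisfaction, work-related problems, views about the organisation and turnover intention". None of the other nine staff measures records departure.
- **Target population:** "A total of 108 staff will participate in the study", which is 36 per condition.
- **Data analysis:** for staff outcomes, "repeated measures multiple analysis of covariance (MANCOVA; controlling for group baseline scores on outcome measures) will be used for our continuous measures". Attrition of 20% is allowed for as a single rate, with the statement that "we will maintain at least 28 staff and 96 residents per condition at 12-month follow-up". Power is computed on those retained numbers, at d = .20.

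**The concern.** A conventional repeated-measures MANCOVA needs a full set of occasions for each person, so someone who leaves before 12 months contributes nothing, even if the post-intervention and 6-month questionnaires were returned. That matters little when loss is unrelated to the outcome, or is equal and of the same kind in each condition. Here the article itself argues otherwise: satisfaction drives leaving, and training changes satisfaction. If that is right, more of the dissatisfied staff are lost from the control facilities than from the trained ones. The control stayers then look better than the control group as a whole, and the comparison understates the benefit on satisfaction and stress, the outcomes in the same hypothesis.

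The second part needs no assumption about missing data. Turnover is named as an outcome that training will improve, but what is listed is intention to leave. That is a reasonable proxy, but someone who has left can no longer report it. Actual departures have no listed place as an outcome.

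**Working it through.** **The plan's own figure.** 108 / 3 = 36 staff per condition; 36 x (1 - 0.20) = 28.8, consistent with the stated minimum of 28. So about 7 to 8 of 36 per condition are expected to be missing at 12 months.

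**Size of the selection effect, using the article's own mechanism.**

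Inputs from the Data analysis section: d = .20 and 20% loss, the latter applied here to the control condition. Assumptions:

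- Satisfaction is standard normal.
- All loss is departure.
- A normal tendency to stay has correlation r with satisfaction, and staff below a fixed threshold on it leave.
- Training affects leaving only through satisfaction, so it shifts the tendency to stay by r x 0.20.
- There is no baseline adjustment.

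Formulas, with z the threshold and p = Φ(z) the proportion leaving:

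- Inflation of the stayers' mean = r x φ(z) / (1 - p).
- Bias in the contrast = inflation in training minus inflation in control.

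Control: p = 0.20, z = -0.842, φ(z) / (1 - p) = 0.280 / 0.800 = 0.350.

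| | r = 1 | r = 0.5 |
|---|---|---|
| Training z | -0.842 - 0.200 = -1.042 | -0.842 - 0.100 = -0.942 |
| Training loss p | 0.149 | 0.173 |
| Training φ(z) / (1 - p) | 0.232 / 0.851 = 0.272 | 0.256 / 0.827 = 0.310 |
| Bias | 1 x (0.272 - 0.350) = -0.08 SD | 0.5 x (0.310 - 0.350) = -0.02 SD |
| Expected stayers' contrast if the true effect is 0.20 | 0.12 | 0.18 |

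Both scenarios respect the stated retention: 28.8 control staff remain, and 36 x 0.851 = 30.6 or 36 x 0.827 = 29.8 trained staff.

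**Equal loss.** With 20% leaving in both conditions by the same mechanism, the two inflations are equal and the bias is zero. A simulation with a baseline correlation of 0.5, baseline-adjusted analysis and a true effect of 0.20 returned estimates of 0.198 to 0.201 for correlations of 0.2 to 0.6 between a poor outcome and leaving.

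**Hypothesis against measure.** The hypotheses and the Discussion speak of turnover. Among the ten staff measures, the only related content is one aspect of the Working Environment Scale: "work-related problems, views about the organisation and turnover intention".

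**The case against.** The strongest objection is that the article never states a complete-case analysis. The sentence on MANCOVA names a model, not an analysis set; the 28 per condition is an input to power, not an exclusion rule; and a MANCOVA can be run on imputed data. Missing-data handling is commonly left to a fuller document, which is not shown. This stands as far as it goes: dropping incomplete records is an inference, and the absence of a missing-data section is not the point. What remains is that the article fixes a method whose usual form discards partial records, for outcomes it says drive leaving.

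A reader might infer a much larger bias by supposing, say, 30% loss in control and 10% in training. The article does not support that. Such a split leaves 36 x 0.70 = 25.2 control staff, and even 25% leaves 27, both below the stated 28. Nor would an effect of d = .20 acting through satisfaction produce gaps that wide. The planned baseline adjustment also changes the size, and no reason is given for the expected 20%, so not all of it need be resignation.

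A reader might also infer that the turnover hypothesis goes wholly untested. That is too strong, because intention to leave tests it indirectly. Finally, a mixed model assumes data missing at random, so it does not by itself answer loss that depends on unobserved satisfaction; and for someone who has left, satisfaction with the facility at 12 months is partly a question of what one wants to estimate. Both points stand, and they are why a sensitivity analysis is needed.

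**Conclusion.** The point holds in a modest form. The named method is a poor choice for staff outcomes that the article expects to influence leaving. Under the article's own mechanism, the bias is about -0.02 SD at a correlation of 0.5 and at most about -0.08 SD, or 10% to 40% of the planned d = .20 (0.02 / 0.20 and 0.08 / 0.20). These figures rest on the assumptions listed above, chiefly 20% control loss, all of it departure, and no baseline adjustment. The direction against training is probable, not certain: other reasons for leaving could reverse it, and equal loss by the same mechanism removes it. That incomplete records would be dropped is inferred, not stated. The mismatch between hypothesised turnover and measured intention can be read directly from the article and depends on none of this.

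**What to change.** 1. Replace the repeated-measures MANCOVA with a likelihood-based mixed model for each staff outcome. Use all available occasions from all 108 staff, in the condition to which their facility was randomised, with baseline adjustment and a facility effect.
2. Record whether each staff participant has left the facility by 12 months. Analyse departure as the turnover outcome, by condition and allowing for facility. Label the scale content as turnover intention, so that the proxy and the event are reported separately. At 20% loss there would be at most about 7 departures per condition (36 x 0.20 = 7.2), so the estimate will be imprecise and should be read with its interval.
3. Because the mixed model assumes data missing at random, add one sensitivity analysis in which leavers are assumed to have worse scores than the model predicts.

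The cost is a little more analysis work, and establishing departure status for non-responders at 18 facilities that are already being revisited. The article does not say that reasons for loss are recorded, so this is a small added data item. Design, sample size and questionnaires are unchanged.
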